## 16.7 Database lock

When all data have been entered and discrepancies solved, clean file will be declared, the database will be locked, the code will be broken and the data will be analyzed.

Interim reports based on unblinded data will be prepared after completion of the 6 weeks visit (Visit 7 [SAD part] and Visit 14 [MAD part] and after completion of the 12 months visits (Visit 10 [SAD part] and Visit 17 [MAD part]; one report with combined 12 months SAD and MAD data). The data for the reports will be produced from exports of the cleaned database but no formal DBL will be performed until after the last subject has performed the last 5-year follow-up assessment. A complete CSR including will be written following the final DBL.

All clinical staff involved in data evaluation and all independent evaluators will be kept blinded to treatment.

## 17 STATISTICAL METHODS AND DETERMINATION OF SAMPLE SIZE

The principal features of the statistical analysis to be performed are described in this section. A more technical and detailed elaboration of the principal features will be presented in a separate Statistical Analysis Plan (SAP), which will be signed and approved prior to each planned interim report.

Analyses of the primary and secondary endpoints will be performed by [REDACTED]

## 17.1 General

Data will be presented using summary statistics in terms of number (N), arithmetic mean, standard deviation (SD), median, minimum and maximum value as appropriate.

Categorical data will be presented as counts and percentages. When applicable, summary data will be presented by treatment, and by assessment time. Individual subject data will be listed by subject number, treatment, and, where applicable, by assessment time.

All descriptive summaries and statistical analyses will be performed using SAS Version 9.4 or later (SAS Institute, Inc., Cary, NC).

Baseline will be defined as the visit with last data collection point prior to the first administration of IMP.

To minimize inter-rater reliability between independent experts, pre-study training and rating sessions will be conducted. The experts will be supplied with photos of wounds to rate. The correlation between the ratings will be analyzed using Kappa statistics. If the correlation between the different experts is below 0.8, new rating sessions will be performed until the correlation is above 0.8.

## 17.2 Determination of sample size

No formal sample size calculation has been performed. The proposed sample size is considered sufficient to provide adequate information for the study objectives.

## 17.3 Analysis data sets

### 17.3.1 *Full analysis set*

The Full Analysis Set (FAS) will consist of all subjects who have been randomized and received at least one dose of IMP. This population will be used as the Safety analysis set.

There will be one FAS for each part.

### 17.3.2 *Per protocol set*

The Per Protocol Set (PPS) will consist of all subjects who have been randomized and completed the study without any major protocol deviations that are judged to compromise the analysis of the data. All protocol violations will be judged as major or minor at the clean file meeting.

## 17.4 Description of study population

### 17.4.1 *Demographics and baseline characteristics*

Descriptive statistics for demographics, weight and height will be presented by treatment and cohort using descriptive statistics and listings.

All data will be listed by cohort and subject.

**17.4.2 Medical/surgical history and prior/concomitant medication**

Medical/surgical history and prior/concomitant medications will be presented by cohort and overall using descriptive statistics and listings.

All data will be listed by cohort and subject.

**17.4.3 Treatment compliance**

The number of subjects treated in each cohort, and their treatments will be tabulated.

All data will be listed by cohort and subject.

**17.5 Analysis of safety endpoints (primary endpoints)****17.5.1 Adverse events**

An overview of all AEs, including SAEs, intensity, relationship to IMP, and deaths will be presented by SOC and preferred term (PT).

Incidence of AEs and SAEs will be summarized by SOC and PT by cohort and overall.

All AE data will be listed by cohort and subject and include the verbatim term entered by the Investigator.

**17.5.2 Physical examination**

Clinically significant and non-clinically significant abnormal findings will be specified and presented by subject and summarized by cohort and visit.

Changes over time will be presented using shift tables.

All data will be listed by cohort and subject.

**17.5.3 Vital signs**

Vital signs (systolic/diastolic blood pressure, pulse and temperature) will be summarized by cohort and visit. Data will be presented with absolute and percent change from baseline.

All data will be listed by cohort and subject.

**17.5.4 12-lead ECG**

All ECGs will be categorized as "normal", "abnormal, not clinically significant", or "abnormal, clinically significant" (as judged by the Investigator) and summarized by cohort and visit using frequency tables.

Changes over time will be presented using shift tables.

All data will be listed by cohort subject.

#### 17.5.5 *Safety laboratory analyses*

Safety laboratory data will be summarized by cohort and visit with absolute and percent change from baseline.

Abnormal, clinically significant values will be summarized separately if considered appropriate.

All data will be listed by cohort and subject.

#### 17.5.6 *Local tolerability*

The following parameters are will be measured for local tolerability:

- Appearance of wound and wound edge (inflammation)
- Condition of skin surrounding the wound (inflammation)
- Hemorrhage
- Amount of exudate present
- Presence of slough/necrotic tissue
- Presence of granulation tissue
- Hypergranulation

Each variable will be presented using frequency tables by cohort, treatment and visit.

Shift tables will also be presented by cohort, treatment and visits if considered appropriate.

Subject assessment of pruritus and pain will be analyzed as above.

All data will be listed by cohort, treatment and subject.

#### 17.5.7 *Anti-drug-antibody analysis*

The incidence, observed proportion of subjects testing positive for ADA, and their titer will be presented by cohort and visit.

All data will be listed by cohort and subject.

### 17.6 *Analysis of secondary endpoints*

#### 17.6.1 *CXCL12 levels in blood and in the wound*

Relationship between dose of activated ILP100-DP and levels of CXCL12 in wound biopsies and blood (SAD part only) will be presented by correlation analysis.

Relationship between dose of activated ILP100-DP and the time course of complete wound healing/closure (SAD and MAD parts) will be presented by correlation analysis.

Actual CXCL12 levels in the wound (SAD only) and in the blood (SAD and MAD) together with absolute and percent change will be presented using summary statistics.

*L. reuteri* R2LC colonies following blood culture will be presented using summary statistics by treatment, visit and cohort.

The colonies will be presented both as actual values and by logarithm scale (10 log).

All data will be listed by cohort, treatment (biopsy data) and subject.

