## 7.2 Secondary objectives

- To investigate local and systemic exposure of CXCL12 and *L. reuteri* R2LC
- To determine the effect of activated ILP100-DP on CXCL12 levels in the wound (biopsy; single ascending dose [SAD] part only) and in blood
- To compare immunohistochemistry and histopathology from wound biopsies after treatment with activated ILP100-DP or placebo (SAD part only)
- To assess the time-course of wound healing
- To assess the occurrence of wound rupture
- To assess scar tissue formation
- To assess propagation of *L. reuteri* R2LC colonies containing the pSIP411 plasmid in the blood, on the skin surrounding the wound and/or in feces

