#### **Treatment phase (Visit 1 to Visit 6)**

Screening (Visit 1) will take place from Day -28 to Day -1. At Visit 2, eligible subjects will be admitted to the research clinic on Day 1 for pre-dose safety assessments and full-thickness wound punching with a biopsy punch (6 mm in diameter) on the ventral aspect of the upper arms (2 wounds/arm). The wounds should be separated by approximately 4 cm. One biopsy per subject will be saved for baseline histopathology analysis using the procedure described in Section 11.8.2. Each wound will be numbered using a permanent marker. Prior to wound punching, subjects will be treated with local anesthesia (injected and/or topical) and the area will be cleaned with antiseptics (70% ethanol). The wound punching procedure will be detailed in a separate manual.

A single dose of the IMP will be topically applied to each of the wounds using a pipette; activated ILP100-DP to 2 wounds on one arm and placebo to the other 2 wounds on the other arm as randomized. There should be 1 hour ( $\pm 10\%$ ) between the last wound punch and the start of IMP application to allow for pre-dose study assessments and hemostasis. Two unblinded persons will take part of the administration process, one will perform the application of IMP and the other one will confirm that the correct treatment is administered to the intended wound, i.e. in accordance with the randomization list. The IMP administration will be documented by video recording. Each wound will be dressed separately using an adhesive, transparent film, isolating the wounds from each other. An elastic, tubular bandage will be used on top of the films. For details on the wound incision and IMP application processes, refer to Section 11.4 and Section 10.6, respectively.

The subjects will be carefully monitored by clinical staff during and after IMP administration and will remain at the research clinic for at least 4 hours after dose. Vital signs and ECG will be checked as detailed in Table 8.1-1. There is immediate access to equipment, qualified staff and an ICU in case of an acute emergency. Up to 2 subjects will be dosed on the same day.

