15. CXCL12 blood sampling at 9:00±2 hours. On Day 2: 24h±2 hours post dose but no later than 11:00. On Day 3 and 14, also plating of blood samples prior to centrifugation for blood culturing, see Section 11.8.1 and Section 11.8.1.2.
16. 48 hours after IMP administration (one biopsy from a CXCL12 treated wound and one from a placebo treated wound)
17. Wound healing assessed by the Investigator (direct observation) and by 3 to 5 independent evaluators using photographs.
18. Wound area assessed by 3 to 5 independent evaluators using photographs and the Image J software (National Institutes of health [NIH]) or equivalent.
19. Baseline wound area measurements based on photos taken after wound punching prior to IMP application.
20. Scar tissue formation assessed by the Investigator (direct observation) and by 3 to 5 independent experts using photographs at Visit 6. Scar tissue formation during the long-term follow-up assessed by the Investigator only. Normal/abnormal and Vancouver scar scale. One assessment per wound.
21. Dressing if indicated.
22. From administration of IMP.
23. Collection of AEs including, but not limited to, mortality, development of any new/recurrent cancer, development of infection, immunogenicity related reactions.
24. For definitions of prior and concomitant medications, see Section 11.3.6.

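### Section 17.6.1 makes no use of the paired active and placebo biopsies to estimate the effect on wound CXCL12, so that objective is answered only in part

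*Protocol*

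**What the plan says.** Protocol Section 7.2 sets the objective: "To determine the effect of activated ILP100-DP on CXCL12 levels in the wound". Section 7.2.1 attaches to it an endpoint on the relationship between dose and CXCL12 level.

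Section 9.9 randomizes SAD treatment by arm within each subject. Table 8.1-1, footnote 16, gives the Day 3 sampling: "one biopsy from a CXCL12 treated wound and one from a placebo treated wound". The only earlier tissue comes from the Day 1 wound punch (Section 8.1.1): "One biopsy per subject will be saved for baseline histopathology analysis".

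For CXCL12, Section 17.6.1 plans:

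- a dose analysis: "Relationship between dose of activated ILP100-DP and levels of CXCL12 in wound biopsies and blood (SAD part only) will be presented by correlation analysis";
- summary statistics: "Actual CXCL12 levels in the wound (SAD only) and in the blood (SAD and MAD) together with absolute and percent change";
- a listing: "All data will be listed by cohort, treatment (biopsy data) and subject".

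Two general rules in Section 17.1 also bear on this: "When applicable, summary data will be presented by treatment, and by assessment time" and "Baseline will be defined as the visit with last data collection point prior to the first administration of IMP".

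Sections 17.6.3 (wound healing) and 17.6.4 (wound area) each name both a dose correlation and a comparison of active with placebo. Section 17.6.1 names only the correlation.

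**The concern.** Section 8.2 says subjects serve as their own controls and that placebo shows what happens without active treatment. For wound CXCL12 the matched placebo biopsy is the natural reference. The product expresses the human chemokine (Section 6.1.2), and the plasma assay measures endogenous and bacterial CXCL12 together (Section 11.8.1.1). The protocol describes no method that separates the two sources in tissue. Yet Section 6.2 justifies the early biopsies by the amount of CXCL12 the bacteria deliver to the wound.

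Three things are left open:

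1. The within-subject pair has no named analysis.
2. The correlation may or may not include placebo wounds. On active biopsies alone it compares doses with each other. It cannot show an effect common to all doses, and dose is confounded with sequential cohort.
3. The reference for the change is not stated. If it is the Day 1 punch, the change compares intact skin with a wound about 48 hours old. It then mixes the response to wounding with any effect of the product.

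At stake is whether 12 pairs of invasive biopsies from healthy volunteers yield a direct estimate of the effect they were taken to measure.

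**Working it through.** **No figure to reproduce.** Section 17.2 reports no sample size calculation, and the protocol gives no SD, effect size or alpha for this endpoint.

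**Inputs from the protocol.** 3 cohorts × 4 subjects = 12 SAD subjects, hence 12 active/placebo pairs. Doses are 5×10⁴, 5×10⁷ and 1×10⁹ CFU/cm².

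**Assumptions.** Each biopsy has SD 1. The two biopsies of a subject have correlation ρ = 0.3, 0.5 or 0.7. Tests are two-sided at 5%. Effects are in SD units, listed from lowest to highest dose.

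**Paired contrast, 1 SD effect at every dose.** The SD of the difference is √(2(1−ρ)), and the noncentrality is √12 / √(2(1−ρ)). The critical t on 11 degrees of freedom is 2.201.

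| ρ | SD of difference | Noncentrality | Detection |
|---|---|---|---|
| 0.3 | 1.183 | 2.93 | 76% |
| 0.5 | 1.000 | 3.46 | 88% |
| 0.7 | 0.775 | 4.47 | 98% |

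**Correlation on the 12 active biopsies.** The critical |r| is 2.228 / √(10 + 2.228²) = 0.576. If all doses have the same effect, the expected level does not depend on dose, so detection equals the 5% error rate.

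**Comparison by simulation** (40,000 runs per setting; ranges cover ρ = 0.3 to 0.7). The first correlation uses log10 dose. The second adds the 12 placebo biopsies as dose zero, using log10(dose + 1).

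| Effect by cohort | Correlation, active only | Correlation, placebo as dose zero | Paired contrast, all 12 |
|---|---|---|---|
| 1, 1, 1 | 5% | 60–63% | 76–98% |
| 0, 1, 1 | 28% | 48–49% | 37–65% |
| 0, 0.75, 1.5 | 46% | 63–67% | 41–69% |

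The dose-zero version ignores the pairing and is conservative when there is no effect. On raw rather than log dose, the active-only correlation falls to 9% in the second row and 37% in the third, so the unstated dose scale also matters.

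**By cohort.** The smallest attainable two-sided signed-rank p is 2 × 0.5⁴ = 0.125 with 4 pairs and 2 × 0.5¹² = 0.0005 with 12. For 80% power a paired t-test needs a mean difference of 2.13 SDs of the differences with 4 pairs and 0.89 with 12. Results by cohort can only be descriptive.

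**The case against.** The case for the protocol has five parts.

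- **The objective is addressed.** Section 7.2.1 defines its endpoint as a dose relationship, and Section 17.6.1 analyses that for biopsies. This stands. A reader might infer that the objective goes unanswered, but the document does not support that; it is answered in part.
- **A view by treatment is available.** Section 17.1 allows summaries by treatment and Section 17.6.1 lists biopsy data by treatment. This also stands, but separate summaries of active and placebo are not an estimate of the within-subject difference.
- **A placebo comparison exists elsewhere.** Section 7.2 has an objective comparing immunohistochemistry and histopathology between active and placebo biopsies. Its endpoints include relative amounts of CXCL12, and Section 17.6.2 leaves the detail to the SAP, which is not at hand. That detail is no gap. The remaining point is that Section 17.6.1 does fix an analysis for CXCL12 level, and it omits the contrast that its neighbouring sections name.
- **The change may not refer to the Day 1 skin.** Section 17.6.1 names no reference, and the Day 1 biopsy is labelled for histopathology. The general baseline definition makes that reading natural but does not settle it. A reader might go on to infer a false-positive rate for a before-after test. No such test is planned, only summary statistics, so the valid point is that the reference is missing.
- **An effect equal at all doses is not what the sponsor expects.** Section 8.3.1 expects little or no effect at the lowest dose and treats similar efficacy across doses as a contingency. This is a fair limit: with a rising effect the correlation is comparable with the paired contrast, and with placebo as dose zero it is sometimes better.

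**Conclusion.** The point holds as an improvement at almost no cost, not as a failure to address the objective. Section 17.6.1 leaves the matched pairs without a named analysis, does not settle whether placebo enters the correlation, and gives no reference for the change.

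The size depends on how the section is read. For a 1 SD effect common to all doses, detection is 5% on active biopsies only, about 60% with placebo as dose zero, and 76 to 98% for the paired contrast. A reader might take the gap between 5% and the paired figure as the general loss. It applies only to the active-only reading with a flat dose response. All these figures rest on the assumed SD, effects and ρ of 0.3 to 0.7.

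The case for the paired estimate does not rest on power alone. It measures the effect named in the objective, and it removes both the subject's own level and any cohort shift shared by the two wounds.

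**What to change.** Add to Section 17.6.1, and carry into the SAP:

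> The effect of activated ILP100-DP on wound CXCL12 is estimated as the within-subject difference between the active and the placebo Day 3 biopsy (a ratio if the data are log-transformed), with a 95% confidence interval pooled over the 12 SAD subjects and descriptively by cohort (n = 4). The dose relationship is presented on this difference as well as on the level, stating whether placebo wounds are included. Any change from the Day 1 intact-skin biopsy is descriptive and is not a treatment effect.

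Both dose presentations are worth keeping. The difference removes shared cohort shifts, but its SD exceeds that of a single biopsy when ρ is below 0.5 (1.183 against 1 at ρ = 0.3). The pooled estimate averages over doses and is diluted if the lowest dose does nothing, which is why it should be shown with the results by cohort.

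The cost is a few sentences. All the biopsies are already scheduled, and no visit, sample or subject is added.

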#### **17.6.2 *Histology analysis***

Histological parameters will be assessed by quantitative or semi-quantitative methods frequently applied in the field. Detailed description of the analysis will be provided in the SAP.

All data will be listed by cohort, treatment and subject.

#### **17.6.3 *Wound healing***

Wound healing will be assessed as yes or no at each visit and presented using frequency tables by treatment, visit and cohort. Dose response relationship will be presented by correlation analysis. Comparison between active and placebo treatment will be performed by non-parametric statistics.

All data will be listed by cohort, treatment and subject.

#### **17.6.4 *Wound area***

The reduction in wound area will be presented using summary statistics by treatment, visit and cohort. Dose response relationship will be presented by correlation analysis. Comparison between active and placebo treatment will be performed by ANOVA.

All data will be listed by cohort, treatment and subject.

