### 8.1.1 *Single Ascending Dose (SAD)*

In Part I of the study, single topical doses of the IMP will be administered in 3 sequential cohorts of 4 subjects. For each subject, activated ILP100-DP and placebo will be randomized to experimentally induced wounds on the left and right arm in a 1:1 ratio (i.e. 2 wounds on one arm will be treated with activated ILP100-DP and 2 wounds on the other arm will be treated with placebo as randomized).

The proposed dose levels are:  $5 \times 10^4$ ,  $5 \times 10^7$  and  $1 \times 10^9$  CFU/cm^2 wound area. The rationale for the starting dose and the planned dose escalation is detailed in Section 8.3.

Subjects will come for 6 visits to the research clinic for screening, treatment and initial follow-up (Visit 1 to Visit 6), see Table 8.1-1 for details. After Visit 6, a 5-year long-term follow-up period (Visit 7 to 14) will be initiated as detailed below.

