14. CXCL12 blood sampling prior to wound punching at 9:00±2 hours, 1 hour post the last wound punch (within 5 minutes of start of IMP application, which should start 1 hour (+/-10% post the last wound punch) and 1 hour (±10%) after the last IMP application.
15. Pre-treatment. The pre-treatment sample should be taken at 9:00±2 hours.
16. Pre-treatment on Day 5, 8, 15 and 19. The pre-treatment samples should be taken at 9:00±2 hours.
17. On Day 3, 5, 8, 15 and 21, also plating of blood samples prior to centrifugation for culturing, see Section 11.8.1 and Section 11.8.1.2.
18. The CXCL12 blood sample should be taken at 9:00±2 hours.
19. Pre-dose Day 1 and pre-dose on Day 19, see Section 11.8.1.
20. Wound healing assessed by the Investigator (direct observation) and by 3 to 5 independent experts using photographs. No assessment by independent experts on Day 17.
21. Wound area assessed by 3 to 5 independent experts using photographs and the Image J software (NIH) or equivalent.
22. Baseline wound area measurements based on photos taken after wound punching prior to IMP application.
23. Scar tissue formation assessed by the Investigator (direct observation) and by 3 to 5 independent experts using photographs Visit 9 to Visit 12. Scar tissue formation during the long-term follow-up assessed by the Investigator only. Normal/abnormal and Vancouver scar scale. One assessment per wound.
24. Day 5, Visit 5.
25. Day 15, Visit 9.
26. At any time between Day 15 and Day 21.
27. Just prior to treatment on Day 2, Day 8 and Day 15.
28. Dressing if indicated.
29. Dressing collection on Day 2 (applied Day 1), Day 3 (applied Day 2).
30. From administration of IMP.
31. Collection of AEs including, but not limited to, mortality, development of any new/recurrent cancer, development of infection, immunogenicity related reaction.
32. For definitions of prior and concomitant medications, see Section 11.3.6.

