## 8.2 Rationale for study design

The European Medicines Agency (EMA) guideline on strategies to identify and mitigate risks for FIH and early clinical trials with IMPs (EMA/CHMP/SWP/28367/07 Rev. 1) has been considered as have the European Directive 2001/18/EC on the deliberate release into the environment of GMOs and the guidance on the environmental risk assessment of genetically modified organisms from the EMA CHMP/GTWP/125491/06. A 5-year long-term follow-up has been included in line with the recommendations given in EMA/CHMP/GTWP/60436/2007.

The SAD/MAD design of the study is based on the aim to study safety, tolerability and exposure of selected doses of activated ILP100-DP in a limited number of healthy volunteers.

The design is adaptive to allow for flexible dose escalation and involves careful monitoring of the subject's well-being. The study will provide important safety and tolerability data and preliminary efficacy data to support the design of further studies, both in healthy volunteers and in patients.

A placebo control will be used to establish the frequency and magnitude of changes in endpoints that may occur in the absence of active treatment. Subjects will serve as his/her own control receiving both placebo and active treatment on the same occasion. The placebo component consist of the ILP100-DP dilution buffer and the activation peptide SppIP. The dilution buffer contains sucrose, which may have a wound healing effect. Recombinant CXCL12 is not used as placebo since the half-life is too short (approximately 6 seconds) to provide clinically relevant data (Laguri *et al.*, 2007; Lambeir *et al.*, 2001). *Lactobacillus* wild-type is not used as placebo since extensive testing in non-clinical studies have shown that it has no effect on wound healing.

Saline (0.9 % NaCl) will be used as a “no treatment” control for several purposes, 1) all wounds must be treated with a solution to keep the blind, 2) all wounds must be exposed to comparable moisture during the study since moisture is a parameter that affects wound healing and 3) NaCl will identify any wound healing properties of sucrose in the dilution buffer used for both ILP100-DP and placebo.

Randomization will be used to minimize bias in the assignment of treatments to wounds.

Blinded treatment will be used to reduce potential bias during data collection and evaluation of endpoints.

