### 9.9 Randomization

The randomization in the SAD part of study will be done by arm, i.e. either active treatment to the right arm and placebo to the left arm or vice versa. Each arm will have 2 wounds which will be on same location on both arms.

The randomization in the MAD part of the study will also be done by arm, i.e. active treatment to 4 wounds to the right arm and placebo and saline to 2 wounds each on the left arm or vice versa. The wounds will be placed on the same location on both arms. For details, refer to Table 9.9-1.

A computer-generated randomization list will be created using SAS Proc Plan, SAS Version 9.4. The randomization list will be kept by the randomizer in a sealed envelope until database lock (DBL). A copy of the randomization list will be kept by an unblinded pharmacist at the site.

Sealed individual, treatment code envelopes will be kept in a locked and restricted area at the research clinic in case of need for emergency unblinding and at [REDACTED]

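### The active-versus-placebo tests for wound area and healing are not tied to the by-arm, within-subject randomization, and no saline comparison is named for the MAD part

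*Protocol*

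**What the plan says.** On design, Section 9.9 states for the first part that "The randomization in the SAD part of study will be done by arm" and for the second that "The randomization in the MAD part of the study will also be done by arm". Table 9.9-1 shows the MAD consequence: one arm carries active on all four positions, while the other carries placebo on two positions and saline on two. Section 8.2 adds: "Subjects will serve as his/her own control receiving both placebo and active treatment on the same occasion". The SAD part has "3 sequential cohorts of 4 subjects" with two wounds per arm, one of which is removed on Day 3. The MAD part has three cohorts of 8 (Section 8.1.2).

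On analysis, Section 17.6.4 says of wound area: "Comparison between active and placebo treatment will be performed by ANOVA". Section 17.6.3 says of healing: "Comparison between active and placebo treatment will be performed by non-parametric statistics". Both sections leave dose-response to correlation and summarize results by treatment, visit and cohort. The wound-area baseline already exists: "Baseline wound area measurements based on photos taken after wound punching prior to IMP application".

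On saline, Section 8.2 lists three purposes: keeping the blind, equal moisture, and a third, that "NaCl will identify any wound healing properties of sucrose in the dilution buffer used for both ILP100-DP and placebo". The same section says the sucrose in the buffer may itself affect healing. Sections 17.6.3 and 17.6.4 name no comparison involving saline.

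**The concern.** All active wounds of a subject sit on one arm and all control wounds on the other. For active versus placebo, the randomized unit is therefore the arm within a subject. A MAD cohort supplies 8 pairs of arms, not 32 active and 16 placebo wounds that vary independently.

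A plain ANOVA can miss this in two ways. With wounds as the unit and no blocking, differences between subjects go into the error term although each subject is their own control. With a subject block but a wound-level residual, wounds on one arm count as independent replicates, and anything shared by an arm is mistaken for treatment.

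The same question arises for dose-response: correlating outcome with dose across cohorts does not use each subject's own placebo, and no dose scale is given. If the placebo buffer may be active, the placebo–saline contrast also matters for reading active versus placebo. Section 8.2 wants the study to give preliminary efficacy data for designing later trials, so the precision attached to these estimates matters even though they are secondary.

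**Working it through.** **Plan's own figures.** None to reproduce. Section 17.2 states that no formal sample size calculation was made, and no variance, effect, alpha or power is given. The two-sided 5% level and all variance shares below are assumptions.

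**Model.** Outcome = subject + arm-within-subject + wound, with variances v_s, v_a, v_w summing to 1. With n subjects, a active and p placebo wounds per subject:

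- true variance of the active–placebo difference = [2·v_a + v_w·(1/a + 1/p)] / n
- variance that a one-way ANOVA on wounds works with, approximately = (v_s + v_a + v_w)·(1/a + 1/p) / n

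**MAD cohort.** n = 8, a = 4, p = 2, so 1/a + 1/p = 0.75. The one-way standard error is √(0.75/8) = 0.306 whatever the shares.

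- Shares 0.5/0/0.5 (subject/arm/wound): true SE = √(0.375/8) = 0.217. The one-way SE is 1.41 times too large.
- Shares 0.1/0.4/0.5: true SE = √((0.8 + 0.375)/8) = 0.383. The one-way SE is 0.80 of what it should be.

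**Simulated type I error, MAD cohort, nominal 5%:**

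| Subject / arm / wound | One-way on wounds | Subject block, wound residual | Paired arm means |
|---|---|---|---|
| 0.6 / 0 / 0.4 | 0.6% | 5.0% | 4.9% |
| 0.5 / 0 / 0.5 | 1.1% | 5.2% | 5.1% |
| 0.4 / 0.1 / 0.5 | 3.5% | 9.7% | 5.0% |
| 0.3 / 0.2 / 0.5 | 6.2% | 13.2% | 5.0% |
| 0.1 / 0.4 / 0.5 | 12.7% | 19.0% | 5.1% |

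**SAD after Day 3.** One wound per arm remains, so blocking on subject is the same as pairing: type I error is 4.9–5.3% in all scenarios run. The unblocked version is conservative (0.9–4.2%).

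**Power, MAD cohort, effect 0.5 SD.**

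- Shares 0.6/0/0.4: one-way about 34%, paired means over all four active wounds about 60%, subject-blocked about 71%. Using only the two active wounds at positions matched to placebo gives about 49%.
- Shares 0.4/0.1/0.5: one-way 37%, paired 36%. Pairing gains no power here; its advantage is a correct error rate.

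**Healing in a SAD cohort.** With 4 subjects, the smallest two-sided p of an exact signed-rank or sign test is 2/2⁴ = 0.125.

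**Dose scale.** The efficiency of a linear dose score is its squared correlation with the true effect pattern. Section 8.3.1 hypothesizes that the lowest SAD dose lies below the therapeutic window and that 5×10⁷ is therapeutic, which suggests effects (0, 1, 1). Raw CFU retains 0.29 in either part. Ranks retain 0.75. Log10 dose retains 0.91 with the SAD doses and 0.85 with the MAD doses. The inactive-low-dose hypothesis is stated for the SAD dose only, so the MAD figure is illustrative.

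**Error terms with saline.** Active versus either control is an across-arm contrast, whose error includes 2·v_a. Placebo and saline share an arm, so v_a cancels. One residual cannot serve both.

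**The case against.** A reader might infer that the protocol prescribes unpaired tests on wounds. It does not. Blocked and split-plot analyses are also ANOVA, signed-rank and McNemar tests are also non-parametric, and correlation includes rank correlation. Section 17 offers only principal features and leaves technical detail to a SAP that is not available here, while Section 8.2 already states the own-control principle. Absent model terms would not by themselves be a fault.

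A reader might also infer that saline was forgotten or that the design was built around it. Neither is right: the sucrose question is one of three stated purposes, and saline is summarized by treatment. In a first-in-human trial whose primary aim is safety, a descriptive placebo–saline result has some value.

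All of this stands, as do two further limits. The variance shares are invented for the calculation. If arm variance is truly zero, a subject-blocked wound-level ANOVA holds its size and has more power than pairing (71% against 60% above).

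What remains is that the protocol does fix the contrast and the class of test, and a SAP could follow that wording to the letter and still be invalid in the MAD part. Adding only a subject block, the obvious repair, is anti-conservative as soon as arms differ. Section 8.2 also says saline will identify a sucrose effect, whereas Section 17.6 makes no such comparison.

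**Conclusion.** The point holds as a specification that should be tightened, not as proof that the planned analysis is wrong. In the MAD part a wound-level ANOVA would give wrong standard errors: type I error of about 0.6–13% without a subject block and 5–19% with one, against about 5% for arm-level pairing. These ranges rest on a two-sided 5% level and on assumed shares with subject 0.1–0.6, arm 0–0.4 and wound 0.4–0.5. A claim that results will be too optimistic, or too weak, is not supported, because the direction turns on variances the protocol does not give. The wound-replication problem does not arise in SAD after Day 3. On saline, the supportable statement is that a named comparison is missing for a question the protocol says saline will answer. The endpoints are secondary, but the correction is cheap and the results are meant to inform later trials.

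**What to change.** - **Wound area.** Replace the plain ANOVA with one of two analyses. (a) A mixed model with random subject and random arm-within-subject, treatment and wound position fixed, baseline wound area as covariate, and denominator degrees of freedom at arm level for active versus control. (b) A paired analysis of each subject's mean over all active wounds minus the mean over placebo wounds. These are different analyses, so name one as the main one. In (b), keep all four active wounds, since restricting to matched positions costs power.
- **Healing.** Use a paired non-parametric test on the per-subject difference in proportion healed. In SAD, pool the cohorts or report descriptively, because 4 subjects cannot reach a two-sided 5%.
- **Saline, MAD only.** Add placebo versus saline as a within-arm contrast with its own error term, and active versus saline across arms.
- **Dose-response.** Relate the within-subject active-minus-placebo difference to log10 or ranked dose.

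The cost is protocol and SAP wording and modest programming; all data are already collected. The price is about 7 error degrees of freedom per MAD cohort (8 − 1), and some lost power compared with a subject-blocked wound-level ANOVA if arms truly do not differ.
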